## Methods/design

### Design and eligibility

The study is a multi-center, cluster randomized controlled, pragmatic trial using parallel groups, with a duration of eighteen months, and four six-monthly assessments. Six nursing homes will participate in the intervention and six will continue care as usual. Randomization will be conducted on the level of nursing homes to prevent contamination bias within the nursing home. The nursing homes will be located throughout the Netherlands, and each will participate with two dementia special care units (DSCUs). In the Netherlands, dementia patients usually reside on DSCUs, and medical care including prescription of psychotropic drugs is provided by an elderly care physician employed by the nursing home [19]. In an investigation preceding the PROPER II study, the observational PROPER I study, the same twelve nursing homes will participate. Nursing homes will be selected based upon their responses on a questionnaire regarding the proportion of patients using psychotropic drugs per individual DSCU. In order to maximize variation in the use of psychotropic drugs in the PROPER II study, those nursing homes, more specifically, those DSCUs with either high or low rates, will be approached for participation. Ideally, six nursing homes with high PDU, and six with low PDU will be included. Since the sample size needed for PROPER II (see below) is lower than for the PROPER I study [20], two DSCUs from each participating nursing home will be randomly included in the current study.

In total, 360 patients with a chart diagnosis of dementia will be included, i.e. on average fifteen patients of each of two DSCUs of twelve nursing homes. From DSCUs with more than fifteen patients, a random selection of fifteen patients will be included, regardless of their PDU. For DSCUs with less than fifteen patients, additional DSCUs will participate to retrieve the warranted number of patients per nursing home. Patients who die or are discharged from the DSCU, will be replaced during the study period. Physicians and nurses who are directly involved in the medical treatment and care for the patients will collect the patient data.

This study is a collaboration between the sections for elderly care medicine of three Dutch university Medical Centers and the Dutch Institute for Rational Use of Medicine [21], and is supported by the Dutch association for residential and home care organizations (ActiZ), and the Dutch Health Care Inspectorate.

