### Statistical analysis

Multilevel analysis will be applied to study the change in the proportion of patients with appropriate PDU between baseline and the average at six, twelve, and eighteen months on intervention DSCUs and control DSCUs, after correction of relevant covariates, such as baseline PDU and NPS. The use of a multilevel model will be applied for a number of reasons: patient PDU is hypothesized to be dependent on the prescription policy of the physician and thus to be nested within DSCUs, the longitudinal design and cluster randomization, and the replacement of drop-outs.

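### Nursing homes are randomised, but the primary analysis and the sample size name only the DSCU as cluster; without a nursing-home level the type I error can exceed 5%

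*Protocol article*

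**What the plan says.** Three sections of the protocol article bear on the unit of analysis.

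- **Design and eligibility** sets the unit of randomisation: "Randomization will be conducted on the level of nursing homes to prevent contamination bias within the nursing home". The split is stated as "Six nursing homes will participate in the intervention and six will continue care as usual". Each home contributes two DSCUs, so there are 12 randomised units and 24 DSCUs, and "In total, 360 patients with a chart diagnosis of dementia will be included".
- **Sample size** uses the word cluster for the DSCU: fifteen patients per cluster, an ICC of 0.05, 21 clusters, and 23 after allowing for loss of DSCUs.
- **Statistical analysis** compares the change in the proportion with appropriate psychotropic drug use "on intervention DSCUs and control DSCUs, after correction of relevant covariates, such as baseline PDU and NPS". Its first reason for a multilevel model is that "patient PDU is hypothesized to be dependent on the prescription policy of the physician and thus to be nested within DSCUs". The same sentence adds further reasons: "the longitudinal design and cluster randomization, and the replacement of drop-outs".

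The nursing home is not named as a level of the model, and no home-level ICC is given.

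**The concern.** In a cluster randomised trial the treatment effect has to be judged against the variation between the units that were randomised. Here these are 12 homes. A model whose highest level is the DSCU judges the effect against 24 units, as if the two DSCUs of a home had been allocated independently. They were not: they always fall in the same arm.

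This does harm only if the two DSCUs of a home resemble each other beyond the intervention, and the article gives reasons to expect that. It attributes the clustering to the physician's prescribing policy, and Design and eligibility states that "prescription of psychotropic drugs is provided by an elderly care physician employed by the nursing home". The education is delivered locally at each intervention home (Component 1), and a local project coordinator organises the work (Intervention). The stated reason for randomising homes, contamination within a home, also concedes that units in one home influence each other.

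At stake are the width of the confidence interval for the primary effect and the false-positive rate of the primary test. With positive home-level correlation, leaving the home out can err only towards too small a standard error.

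**Working it through.** **Step 1. Reproduce the plan's own figure.** Inputs from Sample size: 60% against 80%, alpha 0.05 (two-sided assumed, as the article does not say), power 80%, 15 patients per DSCU, ICC 0.05.

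- Two-proportion formula with continuity correction: 91 patients per arm.
- Design effect: 1 + (15 − 1) × 0.05 = 1.70.
- Total: 2 × 91 × 1.70 = 309.4 patients; 309.4 / 15 = 20.6, so 21 clusters, as stated. Without the continuity correction it would be 82 per arm and 19 clusters.
- Drop-out: 21 × 1.1 = 23.1, shown as 23.

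The stated 21 is reached with the DSCU as the cluster and no term for the home.

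**Step 2. Add the home level.** Let rt be the ICC within a DSCU and rh the ICC between patients in different DSCUs of the same home. The design effect becomes 1 + 14·rt + 15·rh. The article gives rt = 0.05 but not rh, so rh is varied over its possible range.

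| Share of ICC at home level | rh | Design effect | Total N, formula of step 1 |
|---|---|---|---|
| none | 0 | 1.70 | 309 |
| half | 0.025 | 2.075 | 378 |
| all | 0.05 | 2.45 | 446 |

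The planned total is 360.

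**Step 3. Understatement of the standard error.** A simple ratio for the extreme case is √(2.45 / 1.70) = 1.20. A fuller version allows for the fact that the spread of DSCU means within an arm itself picks up part of the home variance:

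- True variance of an arm mean: rh/6 + (rt − rh)/12 + (1 − rt)/180.
- Expected DSCU-level estimate: [rh × 10/11 + (rt − rh) + (1 − rt)/15] / 12.
- All at home level: 0.01361 / 0.00907 = 1.50, square root 1.22.
- Half at home level: 0.01153 / 0.00926 = 1.25, square root 1.12.

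**Step 4. Type I error at a single time point.** Simulation of null trials with 12 homes, 2 DSCUs per home and 15 patients per DSCU, total ICC 0.05:

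| Share of ICC at home level | DSCU-level t test, 22 df | Home-level t test, 10 df |
|---|---|---|
| none | 5.0% | about 5% |
| a quarter | 6.3% | about 5% |
| half | 7.8% | about 5% |
| all | 10.8% | about 5% |

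As a hand check, dividing 1.96 by the factors of step 3 gives tail areas of 7.9% (half) and 11.0% (all), in line with the table.

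**Step 5. Change from baseline.** The planned contrast is the change from baseline to the average of three follow-ups. A home effect that is the same at every assessment cancels from a change; only its unstable part remains. With the whole ICC of 0.05 at home level, a t test on 22 df, assumed stability of the home effect and patient-level stability from 0 to 0.7:

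| Assumed stability of home effect | Type I error |
|---|---|
| fully stable | about 5% |
| 90% | 5.9 to 7.8% |
| 80% | 6.7 to 9.3% |
| 50% | 8.6 to 12.7% |

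With half the ICC at home level and 80 to 90% stability it is 5.4 to 7.0%. The stabilities are assumptions; the article gives none. Replacing patients who leave lowers patient-level stability, which points to the lower end of each range.

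**The case against.** The strongest reply is that the article never says the DSCU is the only level. The sentence gives reasons for using a multilevel model rather than listing random effects, and it names cluster randomisation as a reason separate from nesting in DSCUs. A full analysis plan may contain a home effect and suitable degrees of freedom. That stands. A reader might infer that the home has been left out of the model, and the document does not establish this. But brevity does not explain everything: the units contrasted, the nesting level and the clusters of the sample size are all the DSCU, consistently one level below randomisation. The article states a level, and it is not the randomised one.

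Second, the home-level share of the correlation is unknown. Employment by the home does not mean that one physician serves both DSCUs, and the article selects DSCUs by their own rates of drug use, so it expects variation between units. This also stands, and is why the size is given as a range starting at no inflation.

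Third, the planned outcome is a change from baseline, with covariate adjustment, which can remove much of a stable home effect. This stands too. A reader might take the 11% of step 4 as the trial's actual error rate; the documents do not support any single figure. Nor do they say that a large-sample test will be used, so no inflation from that source is claimed.

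**Conclusion.** The point holds in conditional form. The stated level of analysis does not match the stated level of randomisation. If the model is fitted as described and the DSCUs of a home stay correlated, the primary test is too liberal and its interval too narrow.

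The size rests on three quantities that the article does not give: the home-level share of the ICC, the stability of the home effect over time, and the stability of patients. At ICC 0.05 and one time point the error lies between about 5% and 11%; for change from baseline it lies between about 5% and 13% under the assumed stabilities. Little or no inflation is a possible outcome. An analysis at the randomised level keeps about 5% in every single-time-point scenario examined, so protection does not depend on resolving these unknowns.

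**What to change.** In Statistical analysis, state the model as measurements within patients, within DSCUs, within nursing homes. Include a nursing-home random intercept and a home-by-period term, so that variation between homes in their change enters the standard error of the intervention contrast. Say that these terms are retained even if their estimated variance is small. Test the intervention effect against a small-sample reference with about 10 df (12 homes minus 2 arms), or use a home-level summary analysis as the primary test. If an unseen analysis plan already does this, align the article's wording with it.

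No new data and no change to allocation are needed. The cost is precision. Even with no home-level correlation, moving from 22 to 10 df raises the critical value from 2.074 to 2.228, a factor of 1.07 on the half-width. Where home-level correlation exists, the standard error also grows, by up to the factor of about 1.2. Power falls somewhat: on the plan's own formula 378 or 446 patients would be needed with half or all of the ICC at home level, against 360 planned.

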### Ethics approval

The local Medical Ethics Review Committee ‘CMO Regio Arnhem-Nijmegen’ rated the study (number 2012/226) and pronounced that the study is in accordance with the applicable rules in the Netherlands concerning the review of research ethics committees and informed consent. Representatives of all selected patients will be approached in writing to inform them about the study and to give them the explicit opportunity to refrain from participation of the patient in the study. The study will be conducted in accordance with the Declaration of Helsinki [55].

## Discussion

This protocol presents the design of a cluster randomized controlled trial evaluating the effectiveness of a structured and repeated multidisciplinary medication review supported by education and continuous evaluation to improve appropriate prescription of psychotropic drugs for NPS in nursing home patients with dementia.

The strength of this study’s intervention is the multidisciplinary three-component approach of involving professionals who are educated to carry out a structured and repeated medication review. By including not only the pharmacist and physician but also the nurse, the multidisciplinary team is expected to bring optimal knowledge from different perspectives. In this setting, not only medical and pharmaceutical expertise is taken into account, but also insight into the patients’ NPS, for which the psychotropic drugs are prescribed. Besides, the nurse has close contact with the representative of the patient, which further allows input on wishes regarding treatment or acceptation of NPS for the individual patient to be included in the medication review. Moreover, this study is a broad collaboration between several Dutch parties. Aside from the sections for elderly care medicine of three Dutch university Medical Centers, which have close connections with numerous nursing homes, the Dutch Institute for Rational Use of Medicine, the Dutch association for residential and home care organizations (ActiZ), and the Dutch Health Care Inspectorate are actively involved in this project. This has not only contributed to the design of the study and structure of the intervention, but will also facilitate the knowledge transfer of the results to daily practice after completion of the study. In case effectiveness of this three-component intervention is shown, this medication review method will be used on a broader scale to increase awareness of physicians, pharmacists and nurses of proper psychotropic drug use.

The study may have some limitations. Firstly, the involvement of a pharmacist for medication review is currently starting to become part of usual care, also in the control nursing homes. However, these medication reviews are most likely not introduced in a similar education-based, structured, and multidisciplinary fashion. Secondly, the turn-over of pharmacists, physicians, and/or nurses will affect the knowledge regarding the proposed conduct of the medication reviews, in case new staff did not attend the education sessions. However, due to the pragmatic design, the study will have a large external validity and it is expected that a potential effect is at least not overestimated.

Concluding, in the PROPER II study we target to improve the quality of pharmacological treatment of NPS of nursing home patients with dementia, by implementing a sound intervention of a structured and repeated multidisciplinary medication review supported by education and continuous evaluation.
